## Screening and enrolment

Volunteers who expressed interest in participating in the study will undergo initial screening via a digital survey or phone. The participants will undergo screening for cognitive involvement at the beginning of the baseline assessment, and if found eligible, they continue to complete the baseline assessment. The following procedures will be conducted at the baseline assessment.

### Baseline assessment

Written informed consent will be obtained, and the participants will be subjected to a baseline assessment to complete the questionnaires (age, sex, ethnicity, education, income, employment status, OA duration, pain severity, interference and quality, co-morbidity, psychological states, medication use, and other treatments for OA pain-management activities) (82–84) and undergo anthropometric measurements.

### Allocation

After the baseline assessment, the participants will be allocated into one of the three study groups with equal probabilities. Blocks of unequal length, with the measurements and the possibilities of these lengths unknown to other investigators, will be used to promote allocation concealment. The senior biostatistician, using non-informative group allocation codes, will generate the allocation sequence using a standard computer software.

### Allocation concealment

The allocation of groups will be concealed using opaque envelopes to conceal the sequence until interventions are assigned. The senior biostatistician will prepare the envelopes and provide them to the assistant research fellow (ARF). The ARF will give the opaque sealed envelope to the participants following the baseline assessment. The participants open the envelope to reveal the group they have been allocated to after the baseline assessment. The participants inform the ARF about the group, and the ARF administers one of the active interventions to the participant. If a participant is identified to be allocated to the usual care control group, they would be advised to continue managing their health condition as usual and attend the follow-up assessment sessions.

### Blinding

The outcome assessor and all investigators will be blind to the group allocation. The participants and the intervention provider will not be blinded to the intervention because the content will be evident. The biostatistician will be blinded to the study groups until all planned analyses are completed, thus minimising bias during data analysis. All the participants will be requested to keep their treatment allocation group private from the outcome assessor during the duration of the study. This information is detailed and indicated to the participants within the study information sheet.

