9. **Tailoring** If the intervention was planned to be personalised, titrated or adapted, then describe what, why, when, and how.	The BrainMaster training programme will provide feedback (reward) according to the real-time brain states of the study participants.
10. **Modifications** If the intervention was modified during the course of the study, describe the changes (what, why, when, and how).	Not applicable. This is a protocol for a feasibility trial.
11. **How well** Planned: If intervention adherence or fidelity was assessed, describe how and by whom, and if any strategies were used to maintain or improve fidelity, describe them.	A research assistant providing training will record the number of training sessions attended by participants (i.e., adherence rates). Adherence rates will be summarised at the end of training. An investigator will monitor the fidelity of the intervention.
12. **Actual:** If intervention adherence or fidelity was assessed, describe the extent to which the intervention was delivered as planned.	Not applicable. This is a protocol for a feasibility trial.

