### Outcome measures

The assistant research fellow will collect primary outcome measures throughout the study period. All secondary outcome measures will be collected at baseline, immediately post-intervention (4th week), and 3 months post-intervention by a research assistant (RA-2) blinded to group allocation. The RA will be adequately trained to collect quantitative sensory testing procedures, electrocardiogram, and electroencephalography recordings (Table 2).

**Table 2 T2:** Secondary outcome measures.

Outcome domain and constructs (96–98)	Brief description of measurement tools	Measurement time points
Pain		
Pain severity	The brief pain inventory—short form (pain subscale) Pain severity on a 10-point scale (0 = no pain and 10 = worst pain possible) in the past 24 h, 1 week, and 4 weeks.	T_B,_ T_1m,_ T_3m_
Pain unpleasantness	In the last 2 weeks, how unpleasant has your knee pain been? ‘Not at all’, ‘slightly’, ‘moderately’, ‘very much’, and ‘extremely’.	T_B,_ T_1m,_ T_3m_
Pain bothersomeness	In the last 2 weeks, how bothersome has your knee pain been? ‘Not at all’, ‘slightly’, ‘moderately’, ‘very much’, and ‘extremely’.	T_B,_ T_1m,_ T_3m_
Intermittent and constant pain	The measure of intermittent and constant osteoarthritis pain (11 items). Each item is rated on a 5-point ordinal response scale (Not at all/No constant or intermittent knee pain, Mildly, Moderately, Severely, Extremely).	T_B,_ T_1m,_ T_3m_
Pain quality	PainDETECT questionnaire (12 items). Each symptom is rated on a 5-point ordinal response scale (1 = never to 5 = very strongly). Score classification: ≤12—nociceptive pain, 13–18—possible neuropathic pain, ≥19—likely neuropathic pain.	T_B,_ T_1m,_ T_3m_
Movement evoked pain	Pain severity during a 6-min walk distance and physical performance tasks—rated pain on NPRS on a 0–100 scale (0 = no pain, 100 = the most intense pain imaginable) scale.	T_B,_ T_1m,_ T_3m_
Flare in osteoarthritis	Flare-OA (16 items) patient-reported instrument to assess the occurrence and severity of knee OA in the past 4 weeks.	T_B,_ T_1m,_ T_3m_
Physical functioning		
Pain interference	The brief pain inventory—short form (interference subscale—nine items) evaluate the impact of pain on daily activities Rated on a 10-point scale (0 = no pain and 10 = worst pain possible).	T_B,_ T_1m,_ T_3m_

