Sleep quality and disturbances	Pittsburgh sleep quality index (19 items) assesses sleep quality over a 1-month time interval. Scored 0 (no difficulty) to 3 (severe difficulty). Total score (range 0–21). Higher scores indicate worse sleep quality.	T_B,_ T_1m,_ T_3m_
The participants’ perceptions about interventions and their impact on their health condition/pain.		
Global perceived change	Perceived change in the knee pain when compared to baseline/before training (−5 = much worse, through 0 = unchanged, to +5 = completely, recovered).	T_1m, and_ T_3m_
Acceptability of interventions	Visual analogue scales (0–10) to measure overall acceptability, burden, perceived effectiveness, ethicality, culturally acceptable, research team's trustworthiness and knowledge, and the likelihood of negative side effects of training.	T_B_
Perceived treatment satisfaction and usefulness of training	Rated on a 0–10 NRS; 0—not at all satisfied to 10—highly satisfied.	T1m, and T3m
Credibility/expectancy of the intervention	The credibility/expectancy questionnaire (5 items)	T_B_
Predictors of training		
Level of engagement with the training	Rated on a 10-point ordinal items scale, where 1 = least engaged and 10 = highly engaged.	At every session
Level of motivation	Single-item; rated on a 10-point ordinal items scale, where 1 = least motivated and 10 = highly motivated.	T_B_ and every session
Cost-and-consequences		
Costs	The osteoarthritis cost-and-consequences questionnaire will be used to measure healthcare use/expenses in the past 3 months.	T_B,_ and T_3m_
Quantitative sensory testing, physical performance assessment and physiological recordings		
	Quantitative sensory testing procedures	T_B,_ T_1m,_ T_3m_
	Resting and evoked electroencephalography.	
	Heart rate, blood pressure, and respiratory rates	
	OARSI Minimum physical performance core set	
	Short physical performance battery (SPPB) standing balance tasks.	

T_B_, at baseline; T_1m_, immediately post-intervention (4th week); T_3m_, 3 months post-intervention.

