### Qualitative study

An assistant research fellow will coordinate with the investigators in conducting semi-structured in-depth interviews following the intervention to evaluate participant experiences in the trial (94, 95). As they finish the trial, the participants will be asked if they would consider this additional interview and be enrolled sequentially until numbers are met. The interview will explore experiences and perceptions regarding interventions based on the theoretical framework of acceptability. These would be recorded with the consent of the participants. The aims of this interview include exploring the participants’ experiences regarding the barriers and facilitators in participating in the trial. In addition, the interview aims to assess the acceptability of the research procedures, including the intervention, preferences for the study site, the perceived value of the study, and the acceptability of interventions as potential clinical treatments for managing knee OA. Furthermore, the interview seeks to explore the perspectives of Māori people on assessment and treatment practices that align with their cultural worldview (95). Māori is treated as an important subgroup and are selected and interviewed separately. We aim to interview five people per group with a purposeful sample of Māori participants from each group. The participants in the usual care group will also be interviewed to explore their experiences participating in the trial, including the acceptability of the assessment procedures.

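### Tasks assigned elsewhere in the protocol contradict the claim that all investigators are blind, and leave the blinding of the biostatistician and the outcome assessor unsecured

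*Protocol article*

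**What the plan says.** The Abstract and the Study design section call the trial double-blind, and explain in brackets that this refers to the outcome assessor and the investigators. The Blinding section repeats it without exception: "The outcome assessor and all investigators will be blind to the group allocation". It adds, for the statistician, "The biostatistician will be blinded to the study groups until all planned analyses are completed, thus minimising bias during data analysis". It says openly that participants and the intervention provider are not blind.

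Other sections assign the work as follows.

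- **Sequence and envelopes.** Allocation: "The senior biostatistician, using non-informative group allocation codes, will generate the allocation sequence using a standard computer software". Allocation concealment: "The senior biostatistician will prepare the envelopes and provide them to the assistant research fellow (ARF". The participant opens the envelope, reads the group and tells the assistant research fellow.
- **Fidelity.** Table 1, item 11: "An investigator will monitor the fidelity of the intervention". The Discussion gives the fidelity check of the neurofeedback (NF) delivery to an expert investigator.
- **Interviews.** Qualitative study: the assistant research fellow "will coordinate with the investigators in conducting semi-structured in-depth interviews following the intervention", with a target of five people in each group.
- **Secondary outcomes.** Outcome measures: all of them are collected at baseline, week 4 and 3 months "post-intervention by a research assistant (RA-2) blinded to group allocation". Table 2, which lists them, includes "Perceived treatment satisfaction and usefulness of training" at week 4 and 3 months, and engagement and motivation at each training session. The text under Outcome assessor and blinding adds a motivation questionnaire for the EEG-NF group only.

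**The concern.** A blinding statement tells readers which biases have been guarded against. Here three groups are declared blind, and each has been given at least one task that discloses the arm or may do so.

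Participants know their group, so assessor blinding offers little protection for self-reported outcomes. It matters most for the performance tests, the quantitative sensory testing and the EEG, where the person running the test can influence the result. Analyst blinding matters for the choices made while processing data and fitting models. The protocol plans between-group mixed models and between-group EEG comparisons, and the trial exists to inform a full trial. A blinding scheme that its own task list does not support would overstate protection in the report and could be copied into the full trial.

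**Working it through.** No arithmetic is claimed in the protocol on this point, so the check sets each declared role beside its assigned tasks.

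1. **Investigators.** Declared: all blind. Assigned: fidelity monitoring (Table 1, item 11), NF fidelity assessment (Discussion) and participation in interviews (Qualitative study). Checking how an intervention is delivered requires knowing that the participant receives it. Interviewing people about their intervention discloses the arm, and reaching five per group requires group membership: 3 groups × 5 = 15 of the planned 60 participants. The interviews are offered as people finish the trial. A participant finishes after 3 weeks of training plus 3 months, which is under 4 months, while recruitment runs for 1 year. Interviews with early finishers can therefore take place while others are still in follow-up. The Allocation section also hides block lengths from the *other* investigators, which may mean that the statistician who makes the sequence counts as an investigator; this is suggestive only. Result: direct contradiction.

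2. **Biostatistician.** Declared: blind until every planned analysis is done. Assigned to the senior biostatistician: the coded sequence, then envelopes that reveal the real group. Whoever puts a readable group name in an envelope must be able to translate the code. The non-informative codes therefore do not blind that person. The protocol uses two labels, the senior biostatistician and the biostatistician, and does not say whether they are one person or two. Result: if one person, the claim is false; if two, it could be true, but the text does not say so.

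3. **Outcome assessor (RA-2).** Declared: blind, and collecting all secondary outcomes. Three kinds of item listed as secondary outcomes or described with them are tied to the arm:
   - Satisfaction with and usefulness of training, at both follow-ups. Usual-care participants have had no training to rate.
   - Engagement and motivation at each session. Sessions exist only in the two active arms.
   - The EEG-NF-only motivation questionnaire. Allocation follows the baseline assessment, so this form can be given only once the arm is known.

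   Acceptability and credibility/expectancy are listed at baseline only, before allocation, and do not disclose the arm. Self-report runs through Qualtrics, partly at home and partly in person at the assessment visit. The text does not say in which part the training items fall or whether RA-2 can see them. Result: the assignment conflicts with blinding as written; whether RA-2 would in fact be unblinded is not determined.

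**The case against.** The strongest reply is that the protocol tells the reader plainly who is not blind. Double-blind is defined in brackets, and participants and the provider are said to be unblinded. Assessor blinding also has real safeguards: participants are asked not to disclose their group, questionnaires are electronic and partly done at home, and the success of blinding will be measured. Per-session items cannot in practice be RA-2's job, because RA-2 works at three assessment visits, so assigning RA-2 all secondary outcomes may be loose wording. The two statistician labels may denote two people, and a condensed article can leave that to the full protocol. Investigators do not collect secondary outcomes, and an interview at the end is unlikely to affect that participant's own results.

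Much of this stands. It rules out the readings that no blinding exists, that the assessor could sort all 60 participants by the satisfaction item, or that the analyst is certainly unblinded. The second requires RA-2 to see the answers, and the third requires one statistician in both roles; the document states neither.

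The reply does not remove the conflicts. The bracketed definition of double-blind itself includes investigators, and the fidelity and interview tasks contradict it. Asking participants not to disclose does not cover disclosure through the trial's own forms, and measuring blinding detects failure without preventing it. On the statistician, the article makes a positive claim next to a task that undercuts it, which goes beyond leaving out a detail.

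**Conclusion.** The point holds as a conflict between declared blinding and assigned tasks. It is firm for the investigators. It is conditional for the biostatistician, on whether the person who prepares the envelopes also analyses. For the assessor it is an unsecured risk, conditional on RA-2 being able to see the training-specific items. A reader might infer that the whole blinding scheme fails; the documents do not support that.

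Severity is moderate. The primary outcomes are recruitment, compliance, retention and safety. The feasibility data are collected by the assistant research fellow, who delivers the interventions and is openly unblinded, and no feasibility target depends on a blind analyst or investigator. The effect models are to be read for uncertainty, not significance. What is affected is the credibility of the between-group secondary estimates, above all the assessor-run tests, and the blinding design passed on to the full trial. The size of any resulting bias cannot be calculated from the document.

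**What to change.** 1. **Restate who is blind.** Replace the double-blind description in the Abstract, Study design and Blinding sections with: outcome-assessor-blind; participants, intervention provider, fidelity investigator and interviewing investigators not blind. Acknowledge that self-reported outcomes come from unblinded participants.
2. **Separate the key from the analysis.** Have an existing person who neither analyses, enrols nor assesses hold the code-to-arm key and prepare the envelopes. The statistician then works on dummy-coded arms, with session attendance and EEG-NF-only data held back until the between-group models are done, since those data would identify the arms. If this separation cannot be made, delete the blinded-biostatistician claim.
3. **Keep training items from RA-2.** State that satisfaction, usefulness, engagement, per-session motivation and the EEG-NF-only questionnaire are collected by the unblinded trainer or in a Qualtrics form that RA-2 cannot see. Narrow RA-2's assignment from all secondary outcomes accordingly.

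The cost is protocol wording, a change in who prepares the envelopes and a form-visibility setting, with no new staff. The blinding described will look less favourable. If the registry entry, which was not available, uses the same label, it should be aligned.

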### Interventions

Following the baseline assessment and group allocation, the participants will receive one of the active interventions or the usual care control group. The number of sessions and duration for both interventions will be identical. A trained research assistant will administer both active interventions. A research assistant will be trained to administer the study interventions. Both interventions will consist of 12 20-min sessions which will be administered in four consecutive sessions/week for three successive weeks. The interventions described in this study adhered to the Template for Intervention Description and Replication guide.

### MMT

An MMT regimen (85) will be used. An RA will be trained remotely by the Centre for Mindfulness, University of California San Diego, to conduct the intervention. During each session, the participants will be instructed to focus on the sensation of each breath occurring at the tip of the nose. On progression, the participants will be instructed to broaden their focus to the ‘full flow of the breath’, including bodily sensations. We will instruct the participants to acknowledge thoughts, feelings, and emotions as they arise without judgment and ‘simply return their attention back to the breath sensations’.

### EEG-NF training

An RA will be trained to administer the EEG-NF training using the BrainMaster Inc. system (86). Comby EEG Caps with sensors (Ag/AgCl) are used to record EEG signals (Figure 1). The participants will be instructed to minimise eye blinks, eye/head/neck movements, swallowing manoeuvres, and teeth clenching. The software programme will play a distinct tone when the brain activity of the participants reaches the set threshold of infraslow (0.0–0.1 Hz) frequency band at the pregenual anterior cingulate cortex (pgACC). The participants will be seated and instructed to close their eyes, relax, and listen to the sound feedback. The reward threshold will be adjusted in real time between 60%–80%, which means that the sound feedback will be delivered 60%–80% of the time.

**Figure 1 F1:**
[figure not shown]
A model wearing an EEG Combi Cap.

We will use the EEG- NF programme administered in our pilot studies in people with chronic musculoskeletal pain, including knee OA (64, 65). Infraslow frequency (<0.1 Hz) is a brain electrical rhythm with maximal spectral power in frequencies below 0.1 Hz. Influencing the ISF may normalise electrical activities across resting-state brain networks that are altered in people with chronic pain (87–90). The pgACC is the chosen region of interest (ROI) for the training due to its connectivity with the periaqueductal grey matter (PAG), which promotes endogenous pain inhibition (17, 90, 91). Up-training ISF at the pgACC improved the pain outcomes in people with chronic pain (65). Therefore, the EEG-NF training programme was designed to up-train the ISF at the pgACC to improve pain outcomes through promoting greater sensory modulation, altering attention and cognitive controllability of pain.

The participants in the control group who are receiving usual care will continue to receive treatments as usual. However, they will refrain from practising meditation during the study period. Following the trial completion, they will be offered to receive one of the trainings.

